### Number of patients

The number of patients to be recruited depends on the specific trial hypotheses:i)Randomized comparison of interventional treatment and conservative management:

Interventional management of unruptured brain AVMs suitable to both conservative and curative treatment alternatives will lead to a decrease in the number of poor outcomes (defined as mRS >2) from 25 to 15 % at 10 years.i)Nested trial on the role of embolization in the treatment of brain AVMs:

Pre-surgical or pre-radiosurgery embolization of cerebral AVMs can decrease the number of treatment failures (failure to achieve: (angiographic cure with good outcome)) from 20 % to 10 %.ii)Secondary hypotheses:Curative treatment of cerebral AVMs can be accomplished with an acceptable up-front risk, defined as the occurrence of a treatment-related permanent disabling neurological complication in 10 to 20 % of patients or less (depending on AVM grade).Embolization of cerebral AVMs treatable by surgery or radiosurgery alone can be accomplished with an acceptable risk, defined as permanent disabling neurological complications of 8 % (3.4 to 12.6 %, 95 % CI).

Approximately 540 randomized patients (270 per group) are necessary to detect a hypothesized reduction of 10 % (from 25 to 15 %) in poor outcomes at 10 years, between interventional and conservative groups (all modalities included). It is too early to estimate the number of cross-overs that will occur; with a long follow-up period, losses can be substantial; analyses using the intention-to-treat principle would require a larger number, according to the proportion of cross-overs and losses to follow-up.

In theory, each management strategy should be separately validated, which would mean that for each modality, we would eventually need to recruit 540 patients or more.

For the nested study on pre-therapeutic embolization, 440 patients (220 per group) will be required to detect the hypothesized 10 % increase (from 80 to 90 %) in rate of success, defined as complete AVM eradication without the occurrence of a disabling complication.

### Randomization and allocation of treatment options

Patients will be allocated a management option according to a combination of clinical judgment and randomization, as shown in Fig. 1. Patients for whom interventional management is not indicated will be proposed for conservative management and entered in the registry. Patients presenting with unruptured AVMs (and no other formal indication or contraindication for therapy) and considered for definitive therapy will be allocated interventional treatment or conservative management by randomization (ratio 1:1). The treatment modality to be used in the case of interventional management will be predefined according to clinical judgment prior to randomized allocation stratified according to treatment modality.

**Fig. 1 Fig1:**
[figure not shown]
Treatment allocation. The figure illustrates the list of questions (**a**-**d**) used by the multidisciplinary team to allocate treatments by clinical judgment (**a**-**b**) and/or randomization (**c**-**d**)

Some patients with difficult but ruptured AVMs, or patients that have presented with rupture in the past, but who remain untreated, may also be offered randomized allocation if the treating team judges that they are eligible for both management options.

The interventional therapy arm of the trial involves a plan for eradication of the AVM using: 1) surgical resection when the lesion is considered by a multidisciplinary team to be safely “operable,” or; 2) radiation therapy when the AVM is smaller than 3 cm, and considered to not be safely “operable,” or; 3) curative embolization, when the lesion is considered curable by embolization (with or without adjunct treatments when embolization turns out to be incomplete). Any treatment modality, if judged by the team to be appropriate, can potentially be combined with endovascular embolization.

Patients with AVMs that the multidisciplinary team expects might benefit from endovascular treatment prior to surgical resection or radiation therapy will be pre-randomly allocated to embolization or to no embolization, provided that treatment without adjunct embolization is also felt to be possible.

The patient is registered via a web-based system (http://www.medscinet.com/tobas) that will structure the forgoing allocation process and immediately communicate the result of the randomization (when appropriate) to the multidisciplinary team. The web-based platform is available 24 hours a day and assures concealment of the sequence until interventions are assigned. The first randomization will be stratified according to intended primary interventional management groups (surgery, radiation therapy, or embolization). A minimization algorithm will be used to ensure balance between groups with respect to: 1) presentation (hemorrhagic (Group I) versus all other presentations (Group II)); 2) according to SM AVM grade (I–II versus III–V). After the patient has been pre-randomized and placed in the appropriate arm of the study, the treatment team will verify that the intended management course is appropriate and considered optimal care for the patient. The patient will then be presented the recommendations of the multidisciplinary team (including the allocation by randomization when appropriate) and will be offered participation. There will be full disclosure of the pre-randomized nature of the study (Zelen’s design [44, 45]) to the patients, when this procedure will be used. They will then be asked to sign the consent form. Patients not willing to comply with the proposed allocation will still be offered participation in the study, but a cross-over will be recorded. Patients treated according to clinical judgment alone will be entered in the registry portion of the study (after the consent form is signed).

Justification of stratification, minimization criteria and other design choices such as Zelen’s are provided in Additional file 1.

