### Statistics

There are many components to this study (Table 2). It is important to distinguish the two randomized levels, which will be analyzed separately as randomized trials (intention-to-treat and per-protocol), and the registry portion, analyzed as an observational study.

**Table 2 Tab2:** Predefined group and subgroup analyses according to treatment allocation

Stratified randomized allocation	Groups: Intervention group versus Observation group
	Surgery subgroup versus Observation subgroup
	Radiosurgery subgroup versus Observation subgroup
	Embolization subgroup versus Observation subgroup
Randomization on pre-embolization	Groups: Embolization versus No embolization
	Embo + surgery subgroup versus Surgery alone subgroup
	Embo + radiosurgery subgroup versus Radiosurgery subgroup
Registry	
	Conservative management
	Surgical treatment (alone)
	Surgical treatment (with embolization)
	Radiotherapy (alone)
	Radiotherapy (with embolization)
	Embolization (alone)
	Embolization + surgery
	Embolization + radiotherapy
According to presentation	Unruptured AVM patients
	Ruptured AVM patients
According to SM grading	Low-grade AVM patients
	High-grade AVM patients

*AVM* arteriovenous malformation, *SM* Spetzler-Martin

Descriptive tables on demographic variables and potential risk factors will be provided to describe the groups at baseline. Continuous variables will be summarized in tables and will include the number of subjects, means, standard deviations, medians, minima and maxima. Categorical variables will be presented in tables as frequencies and percentages.

For the first RCT (interventional or conservative management strategy), the primary analysis, concerning the primary outcome (mRS > 2 or death from any cause at 10 years) of unruptured AVM patients will be analyzed using a Fisher’s exact test and the odds ratio with 95 % confidence interval will be reported. The same analysis will be performed for the ruptured group (considered a secondary analysis). All other secondary objectives and analyses for this first RCT will be analyzed in the same way.

The primary outcome of the second RCT (complete obliteration of the AVM combined with a mRS < 3; pre-surgical or pre-radiation embolization versus no embolization) will be analyzed with a logistic regression adjusted for ruptured status and intervention. Adjusted odds ratio and 95 % confidence interval will be reported. Moreover, stratified results by ruptured status and intervention will be presented.

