### Ethics approval

The Institutional Review Board (CER) of the *Centre Hospitalier de l’Université de Montréal* (CHUM) approved the protocol on 22 October 2013 (Study ID: 13.315). Secondary approval will be obtained from all local ethics committees. Recruitment will not begin in any individual center until all local ethical approvals have been obtained. Based on the Declaration of Helsinki, written informed consent will be obtained from each participating patient or appropriate surrogate in oral and written form prior to enrollment.

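### A second suitability check, made with the allocated arm known and before consent, has no stated retention rule, so arm-dependent loss from the randomised comparison is possible

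*Protocol article*

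**What the plan says.** Suitability is first judged before allocation. The Patients section limits the first RCT to unruptured AVMs considered for cure with no contraindication to intervention, and the nested RCT to patients treatable with or without embolization. The section on randomization and allocation of treatment options has the modality fixed by clinical judgment before the allocation. It also asks that ruptured cases offered randomization be eligible for both managements.

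The web-registration paragraph of that section, after Fig. 1, then gives this order:

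1. The system will "immediately communicate the result of the randomization (when appropriate) to the multidisciplinary team". It "assures concealment of the sequence until interventions are assigned".
2. A check follows the allocation ("After the patient has been pre-randomized and placed in the appropriate arm of the study, the treatment team will verify"). Its content is that "the treatment team will verify that the intended management course is appropriate and considered optimal care for the patient".
3. The recommendation, including the allocation, is presented to the patient.
4. "They will then be asked to sign the consent form".

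A patient unwilling to follow the allocation is still offered participation and counted as a cross-over. The paragraph closes with the registry: "Patients treated according to clinical judgment alone will be entered in the registry portion of the study". The Ethics approval section states that "written informed consent will be obtained from each participating patient or appropriate surrogate in oral and written form prior to enrollment". The Statistics section describes the two randomised levels as ones "which will be analyzed separately as randomized trials (intention-to-treat and per-protocol".

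**The concern.** Concealment, as described, ends at assignment. The second check comes after that point, when the only new information prompted by the procedure is the arm. Asking whether a known course is optimal can draw a different answer for the same patient depending on which arm came up. The Discussion describes strong clinician beliefs and treatment risks that vary widely between patients, so such answers are plausible.

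The patient has not yet consented and so is not yet enrolled. If a negative answer means that the patient is not enrolled, the exit is an exclusion after randomisation that depends on arm and probably on prognosis. Patients lost in this way have no 10-year outcome in the trial, and adjustment cannot fully repair the comparison. The paragraph does not separate the two RCTs, so the gap applies wherever pre-randomisation is used.

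**Working it through.** **The plan's own figure.** For 25% versus 15% poor outcome, two-sided 5% and 80% power (power and sidedness are inferred, since the article states neither):

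- Uncorrected n per arm = [1.96·√(2·0.20·0.80) + 0.842·√(0.25·0.75 + 0.15·0.85)]² / 0.10² = 250.
- With continuity correction: (250/4)·[1 + √(1 + 4/(250·0.10))]² = 270 per arm, 540 in total.

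The stated 540 is reproduced. It is used below only as the scale; the point does not dispute it.

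**Who is retained, by type of exit after allocation.**

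| Event after the arm is known | Stated consequence |
|---|---|
| Patient consents but will not follow the allocation | Stays in, cross-over recorded |
| Patient declines to sign at all | Not enrolled; inherent in consent after allocation |
| Team judges the allocated course not optimal | None stated |

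The third row is the gap.

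**What removal would do.** Let p be the true risk in both arms (no treatment effect), f the fraction removed from the interventional arm and r the risk of those removed. The observed risk in that arm is (p − f·r)/(1 − f), so the spurious difference is f·(p − r)/(1 − f). It is zero when r = p.

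*Illustration A.* All inputs are assumptions: p = 20%, and 30% of patients are high-risk with 35% poor outcome. The remainder then have (0.20 − 0.30·0.35)/0.70 = 13.6%. With 270 allocated per arm and the planned Fisher's exact test:

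| Removed from the interventional arm | Observed risk | Spurious difference | Two-sided rejection |
|---|---|---|---|
| None | 20.0% | 0 | 3.9% |
| One third of high-risk (10% of arm) | (0.20 − 0.10·0.35)/0.90 = 18.3% | −1.7 points | 6.8% |
| Half of high-risk (15% of arm) | (0.20 − 0.15·0.35)/0.85 = 17.4% | −2.6 points | 10.6% |

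Rejection rates are exact binomial calculations with 243 and 230 patients left in the interventional arm.

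*Illustration B.* Range check with p = 25%, normal approximation, nominal 5%; the removal fractions and r are again assumptions:

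| f | r = 25% | r = 40% to 60%: spurious benefit | Rejection |
|---|---|---|---|
| 5% | 0 | 0.8 to 1.8 points | 5.5% to 7.8% |
| 10% | 0 | 1.7 to 3.9 points | 7.2% to 18.0% |
| 20% | 0 | 3.8 to 8.8 points | 16% to 66% |

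The sign depends on who leaves and from which arm. Removing high-risk patients from the conservative arm would bias against intervention.

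**What retention would cost.** If the same patients stay in as one-arm cross-overs and take the other arm's risk, the 10-point difference becomes 10·(1 − c) points for cross-over fraction c. Power at 270 per arm (normal approximation, uncorrected) falls from 83.0% to 78.6%, 73.7%, 68.4% and 62.7% at c = 5%, 10%, 15% and 20%. With the continuity-corrected formula that gives 540, restoring 80% power needs 674 patients in total at c = 10% and 760 at c = 15%.

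**The case against.** The strongest reply is that eligibility is decided before allocation, as the Patients section and the earlier paragraphs on allocation show, so the later step only confirms it. This stands in part. It would be wrong to say that eligibility is judged only once the arm is known. But a confirmation that can be answered in the negative with the arm visible still opens an exit.

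A reader might infer that rejected patients leave the RCT and reappear in the registry. The article does not say so. Its registry sentence concerns patients managed by clinical judgment alone, and a pre-randomised patient is not clearly one of these. What is missing is a rule for a negative answer; no exclusion is described.

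A reader might also count patients who refuse to sign on hearing the arm. That loss comes from the disclosed Zelen design, justified in an additional file not shown, and moving the team's check would not prevent it.

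Protections do exist. Unwilling patients are retained as cross-overs, Number of patients refers to the intention-to-treat principle and to a larger sample if cross-overs occur, and Trial monitoring has the safety committee watch cross-overs. None of these reaches a patient whom the team rejects before enrolment.

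Finally, an article may leave to the full protocol which analysis is primary, who exactly is in the intention-to-treat set, and any log of non-consent. That is accepted, and none of it is part of this point. The order of the steps is different, because the article itself states it.

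**Conclusion.** The point holds in a limited form. The stated procedure includes an unblinded suitability check after allocation and before consent, and no stated rule retains a patient who fails it. Arm-dependent exclusion after randomisation is therefore permitted, though not prescribed.

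The stronger reading, that the randomised comparison has lost its protection or is biased, is not supported. No exclusion is described, and the document gives no removal rate, risk profile or direction. The figure of 1.7 to 2.6 spurious points, about a sixth to a quarter of the 10-point target, rests wholly on assumed removal of 10% to 15% from one arm, all at 35% risk against a 20% average. It vanishes if those removed have average risk. It shows that modest selective loss could matter, not that it will occur.

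**What to change.** In the section on randomization and allocation, place the team's confirmation ahead of the display of the arm. The web system should require the team to record and lock that the patient is suitable for both options, and the planned modality, before it shows the allocation. The post-allocation verification sentence can then be removed. Add one sentence: if the team still changes the course after allocation, a cross-over is recorded and the patient is analysed by pre-randomised allocation as far as consent permits.

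This changes the order of a web form and one protocol paragraph. Pre-randomisation and consent after allocation stay as they are, and no clinical rule changes. The downside is the dilution shown above, which the plan already anticipates when it says that cross-overs would require a larger sample. Trial status reports 80 patients recruited and one recruiting center, so the change can precede most enrolment in the randomised comparisons.

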### Planned patient follow-up and data collection

All patients will be seen in clinic 6–8 weeks after treatments, at 6 months, 1 year, and yearly thereafter, as part of routine follow-up care. These intervals will serve to determine mRS scores, and to inquire about possible neurological events and hospital admissions. Patients treated by embolization or surgery are typically followed up with catheter angiography 3 months after the last treatment session, to prove definite eradication of the lesion. Patients treated by radiosurgery are typically followed up by yearly magnetic resonance angiogram (MRA) and catheter angiography 2–3 years after irradiation. Patients managed conservatively are typically followed-up by MRA at yearly intervals, with the interval to non-invasive imaging increasing with time and demonstrated stability. Thus all patients will have invasive or non-invasive imaging (computed tomography angiogram (CTA) or MRA) 3 months to 3 years post-treatment (depending on treatment modality) to determine the presence of a residual nidus. This follow-up is considered to be standard of care. A minimal follow-up imaging program, in treated or untreated patients, should include MRI and MRA at 1, 5 and 10 years. We have minimized the number of tests and visits for patients. The case report forms (CRFs) can be filled at the time of standard clinical visits. There is no extra test, risk or cost beyond what is considered normal care (Table 1).

**Table 1 Tab1:** Schedule of evaluation

Evaluation	Screening	Pre-entry	Entry	Treatment	Discharge	6 months and yearly	10 years
Documentation of AVM	X						
Imaging^a^	X					X	X
Informed consent			X				
Medical treatment/history		X					
Clinical assessment		X				X	X
Neurological exam		X				X	X
Failure to occlude AVM				X			
Number of days in hospital					X		
Discharge disposition					X		
Residual nidus						X	X
Hemorrhage during FU						X	X

^a^Including catheter or non-invasive angiography and brain magnetic resonance imaging (MRI) imaging whenever clinically indicated

*AVM* arteriovenous malformation, *FU* follow-up

### Statistics

There are many components to this study (Table 2). It is important to distinguish the two randomized levels, which will be analyzed separately as randomized trials (intention-to-treat and per-protocol), and the registry portion, analyzed as an observational study.

**Table 2 Tab2:** Predefined group and subgroup analyses according to treatment allocation

Stratified randomized allocation	Groups: Intervention group versus Observation group
	Surgery subgroup versus Observation subgroup
	Radiosurgery subgroup versus Observation subgroup
	Embolization subgroup versus Observation subgroup
Randomization on pre-embolization	Groups: Embolization versus No embolization
	Embo + surgery subgroup versus Surgery alone subgroup
	Embo + radiosurgery subgroup versus Radiosurgery subgroup
Registry	
	Conservative management
	Surgical treatment (alone)
	Surgical treatment (with embolization)
	Radiotherapy (alone)
	Radiotherapy (with embolization)
	Embolization (alone)
	Embolization + surgery
	Embolization + radiotherapy
According to presentation	Unruptured AVM patients
	Ruptured AVM patients
According to SM grading	Low-grade AVM patients
	High-grade AVM patients

*AVM* arteriovenous malformation, *SM* Spetzler-Martin

Descriptive tables on demographic variables and potential risk factors will be provided to describe the groups at baseline. Continuous variables will be summarized in tables and will include the number of subjects, means, standard deviations, medians, minima and maxima. Categorical variables will be presented in tables as frequencies and percentages.

For the first RCT (interventional or conservative management strategy), the primary analysis, concerning the primary outcome (mRS > 2 or death from any cause at 10 years) of unruptured AVM patients will be analyzed using a Fisher’s exact test and the odds ratio with 95 % confidence interval will be reported. The same analysis will be performed for the ruptured group (considered a secondary analysis). All other secondary objectives and analyses for this first RCT will be analyzed in the same way.

The primary outcome of the second RCT (complete obliteration of the AVM combined with a mRS < 3; pre-surgical or pre-radiation embolization versus no embolization) will be analyzed with a logistic regression adjusted for ruptured status and intervention. Adjusted odds ratio and 95 % confidence interval will be reported. Moreover, stratified results by ruptured status and intervention will be presented.

The patients entered in the registry will be included in secondary analyses designed to estimate treatment morbidity for each modality and natural history of untreated patients, just as an observational study, for unruptured and ruptured AVMs, for high-grade and low-grade lesions. There are four groups and eight registered subgroups (Table II). Predetermined subgroups that will be examined include: 1) according to treatment modality; 2) according to presentation (hemorrhagic versus all other presentations) and 3) according to SM AVM grade (I–II versus III–V). With a 10-year follow-up, it is likely that there will be losses to follow-up, but it is too early to estimate how many. Primary analyses will include three categories (good outcome; bad outcome; lost to follow-up). We will explore results when a best case scenario (patients lost to follow-up have a good outcome) and a worst case scenario (they have a bad outcome) are imputed.

All analyses will be done with SAS software (SAS Institute Inc., Cary, NC, USA) using a significance level of 5 %.

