**Methods/Trial design:**

TOBAS is a pragmatic, prospective, multicenter, randomized, controlled trial and registry which offers a care trial context for brain AVM patients, including surgical resection, radiosurgery or endovascular embolization, alone or combined. The study includes two RCTs and a multimodality prospective registry. The objectives of the proposed study are to assess whether preventive interventions (surgery, embolization, radiation therapy, alone or combined), selected by the local treatment team and performed as locally practiced, randomly allocated and compared with conservative management, in unruptured brain AVM patients eligible for active or conservative management, can improve the proportion of patients having an independent outcome (modified Rankin Scale (mRS) < 3, as assessed by a standardized questionnaire administered by non-masked care personnel) at 10 years. All patients judged ineligible for randomized allocation are to be entered in a multimodal registry. The objective of a nested trial in patients with ruptured or unruptured AVMs to be treated by surgery or radiation therapy, is to assess whether pre-surgical or pre-radiation embolization, randomly allocated and compared with no embolization, can improve the proportion of patients with complete eradication of the AVM, as locally adjudicated, combined with a good clinical outcome (mRS < 3). The study will require up to 2000 patients in approximately 30 centers or more, followed for 10 years. TOBAS is registered at clinicaltrials.gov: NCT02098252 as of 25 March 2014.

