### Objectives

The general objective of the TOBAS trial is to offer a care trial context for the management of patients with brain AVMs (ruptured or unruptured) [41].

The primary objective of the first randomized study is to compare the effect of conservative versus interventional management (i.e. neurosurgery, radiosurgery, embolization, alone or combined) on a composite of disabling stroke or death from any cause at 10 years in patients with unruptured AVMs (patients with ruptured AVMs will be analyzed separately in secondary analyses).

The primary objective of the second randomized study is to compare the effects of embolization prior to neurosurgery or radiotherapy versus neurosurgery or radiotherapy alone, in the management of patients with ruptured or unruptured AVMs, on a composite outcome of complete obliteration of the AVM combined with an independent functional outcome at the end of the management plan.

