### Outcomes

The primary outcome of the first RCT and of the registry is a composite of disabling stroke (resulting in modified Rankin Scale (mRS) > 2) or death from any cause at 10 years. Functional outcome status will be measured by the modified Rankin Scale, the most widely used outcome measure for stroke [43], using a standardized questionnaire administered by unblinded care personnel.

Secondary outcomes include overall mortality (all causes), overall morbidity (mRS > 2; all causes) at 1, 5 and 10 years, the occurrence of any neurological event during follow-up, the incidence of permanent (more than 3 months) disabling (mRS > 2) peri-operative (within 31 days) complications, the incidence of any peri-operative (within 31 days) complication, the incidence and number of hospital admissions, peri-treatment hospitalization lasting more than 15 days, discharge to a location other than home, occurrence of an ICH after enrollment and for up to 10 years, and occurrence of failure to eradicate the AVM (as determined by angiography) using the intended treatment modality.

The primary outcome of the nested RCT on pre-surgical or pre-radiation embolization is complete obliteration of the AVM (judged by local angiographers) combined with an independent functional outcome (mRS < 3; using a standardized questionnaire administered by unblinded care personnel) at the end of the management plan (no less than 3 months after the last procedure; no more than 3 years after radiation therapy).

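### The first RCT's primary outcome is defined in two incompatible ways: disabling stroke or death in Objectives and Outcomes, but mRS > 2 or death at 10 years, with no stroke requirement, in the Abstract, Number of patients and Statistics

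*Protocol article*

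**What the plan says.** All places are in the Protocol article.

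Two sections require a stroke:
- Objectives compares the arms "on a composite of disabling stroke or death from any cause at 10 years in patients with unruptured AVMs".
- Outcomes gives the first RCT, and also the registry, "a composite of disabling stroke (resulting in modified Rankin Scale (mRS) > 2) or death from any cause at 10 years".

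Three sections do not:
- Abstract, Methods/Trial design: the question is whether intervention "can improve the proportion of patients having an independent outcome (modified Rankin Scale (mRS) < 3" at 10 years. This is the complement of mRS > 2 or death.
- Number of patients: the hypothesis is a "decrease in the number of poor outcomes (defined as mRS >2) from 25 to 15 % at 10 years".
- Statistics: the primary analysis is described as "concerning the primary outcome (mRS > 2 or death from any cause at 10 years) of unruptured AVM patients", by Fisher's exact test.

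The Discussion also describes the endpoint as death and dependency.

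The secondary outcomes in Outcomes include mortality and, separately, "overall morbidity (mRS > 2; all causes) at 1, 5 and 10 years". The mRS is collected by a standardized questionnaire given by unblinded care personnel.

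**The concern.** A primary outcome has to sort every patient into event or non-event in one way only. Here the objective names one rule, and the sample size and test use another. Patients whose disability does not come from a stroke are counted by one rule and not by the other.

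The stake is the status of the main result. Both versions can be derived from the planned data, they need not agree, and the article lets either be called prespecified. Assessment is unblinded, and the stroke version adds a judgement on whether a stroke caused the disability. Fixing the choice before anyone sees results is therefore more than editorial tidiness.

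**Working it through.** **1. Are these the same endpoint in different words?** Set the rules against patient types:

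| Patient | Stroke with mRS > 2, or death (Objectives, Outcomes) | mRS > 2 or death at 10 years (Statistics) |
|---|---|---|
| Dead by 10 years | event | event |
| mRS > 2 at 10 years because of a stroke | event | event |
| mRS > 2 at 10 years from intractable seizures, another illness or a deficit present at entry | no event | event |
| Disabling stroke early, mRS 2 or less at year 10 | event only if strokes at any time within 10 years count | no event |

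The third row separates the definitions on any reading. Such patients are plausible here: Background mentions intractable seizures and focal deficits as presentations, and Eligibility criteria admits any patient with a brain AVM. The fourth row is conditional, because Outcomes does not say whether the 10 years is a window for strokes or the time at which status is read.

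**2. The plan's own figure.** Inputs from Number of patients: 25% v 15%, 270 per group. From Statistics: 5% significance level. Assumed, because not stated: two-sided test, 80% power.

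- Uncorrected: n = [1.960 × √(2 × 0.20 × 0.80) + 0.842 × √(0.25 × 0.75 + 0.15 × 0.85)]² / 0.10² = (1.109 + 0.472)² / 0.01 ≈ 250 per arm.
- With continuity correction: n' = (250/4) × [1 + √(1 + 4/(250 × 0.10))]² = 62.5 × (1 + 1.077)² ≈ 270 per arm, 540 in total.

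This matches the article. Exact Fisher power at 270 per arm is 80.6%. The arithmetic is sound, and because Number of patients defines poor outcome as mRS > 2, it is sized for the endpoint that Statistics tests (taking death as mRS 6).

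**3. What the other definition would do.** The article gives no rate of mRS > 2 without stroke. Let q be an assumed level of such dependency, unaffected by treatment.

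- Reading (a): 25/15% are mRS > 2 rates, as Number of patients words them. The stroke composite is then 25% − q v 15% − q. At q = 5%: 20% v 10%.
- Reading (b): 25/15% are stroke-or-death rates. The mRS > 2 or death endpoint is then p + (1 − p)q in each arm. At q = 5%: 0.25 + 0.75 × 0.05 = 28.75% v 0.15 + 0.85 × 0.05 = 19.25%, a difference of 9.5 points.

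| q (assumed) | (a) stroke composite | Fisher power, 270/arm | total N for 80% | (b) mRS > 2 or death | Fisher power, 270/arm | total N for 80% |
|---|---|---|---|---|---|---|
| 2% | 23 v 13% | 83.7% | 502 | 26.5 v 16.7% | 76.4% | 592 |
| 5% | 20 v 10% | 88.8% | 438 | 28.75 v 19.25% | 70.4% | 674 |
| 10% | 15 v 5% | 97.1% | 320 | 32.5 v 23.5% | 61.2% | 824 |

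N is continuity-corrected, two-sided 5%. Under (a) the 10-point difference is kept at lower rates, so power rises. Under (b) the difference shrinks and the rates move towards 50%, so power falls.

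**The case against.** The best defence is that the short form in Statistics is shorthand for the definition in Outcomes, and that the words on any cause there may attach only to death. That is conceivable, but it does not hold up well. Outcomes itself lists all-cause mRS > 2 apart from the primary outcome, so the article treats the two as different. No section limits the mRS > 2 in Number of patients or Statistics to stroke.

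A second defence is that the article leans clearly one way: Abstract, sample size, analysis and Discussion all use functional status. This stands. It makes the repair easy, but it does not remove the conflict with the stated objective and the formal outcome definition.

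Three stronger conclusions might be inferred, and the article does not support them:
- *The trial is underpowered.* This needs reading (b), which the wording of Number of patients supports least. On the wording as it stands, sample size and analysis match at 80.6%, and reading (a) gives the stroke composite more power.
- *The primary analysis merely tests secondary outcomes.* Mortality and morbidity are listed separately as secondary outcomes, but their composite is not. Sharing components with secondary outcomes is normal for a composite.
- *The definitions disagree in both directions.* The recovered-stroke patient differs only if strokes at any time within 10 years count. If Outcomes means stroke-caused status at year 10, the disagreement runs one way, through non-stroke dependency.

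**Conclusion.** The inconsistency is real and concerns the primary outcome, so it must be resolved. It rests on the plain text and on no assumption beyond some patients being dependent at 10 years for reasons other than stroke.

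Its numerical size cannot be fixed from the article. The figure of 540 is right for 25% v 15% and belongs to mRS > 2. If the stroke composite is the intended primary outcome, its planning rates are not given. With an assumed 2 to 10% non-stroke dependency, equal in both arms, power for that composite is about 84 to 97% if 25/15% are mRS > 2 rates. If they are stroke-or-death rates, power for mRS > 2 or death is about 76 to 61%. The direction is open. The defect is the unsettled definition, not a shortfall in sample size.

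**What to change.** Use one primary definition, word for word, in the Abstract, Objectives, Outcomes, Number of patients and Statistics.

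- **Simplest course:** change Objectives and Outcomes to mRS > 2 or death from any cause at 10 years, the endpoint already sized and analysed. Keep disabling stroke or death as a named secondary outcome. The sentence in Outcomes also governs the registry, so settle both together. Sample size and test stay as they are.
- **If the stroke composite is to be primary:** change the Abstract, Number of patients and Statistics instead. State whether strokes at any time within 10 years count, when the post-stroke mRS is read, and how disability is attributed to stroke under unblinded assessment. Give planning rates for that endpoint and recompute N from them.

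The cost is a wording amendment, plus a new sample-size statement in the second case. No new data are needed: the follow-up section already plans yearly visits for mRS scores and neurological events, and mortality is already an outcome.
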